#### Outcomes

Admissions to hospital for asthma, all-cause anaphylaxis, food anaphylaxis, anaphylactic reaction to *Hymenoptera* stings (hereafter referred as venom), all-cause urticaria, atopic dermatitis and ‘allergy’ will be ascertained from the WA Hospital Morbidity Data Collection and the NSW Admitted Patient Data Collection.

These datasets contain the dates of admission and separation (i.e. discharge, transfer or death), the primary diagnosis and codes for diagnostic procedures performed during hospital stay [22]. In addition, up to 20 secondary diagnoses for children born in WA, and up to 50 secondary diagnoses for children born in NSW are also provided [22]. Clinical diagnoses were coded using the ICD system (ICD-9 CM and ICD-10 AM) [22]. These diagnostic codes are listed in Table 1.

**Table 1 pone.0260388.t001:** ICD-9 CM and ICD-10 AM diagnostic codes of interest.

Outcome	ICD-9 CM codes	ICD-10 AM codes
Asthma	493, 493.0, 493.00, 493.01, 493.02, 493.1, 493.10, 493.11, 493.12, 493.82, 493.2, 493.8, 493.9, 493.90, 493.91, 493.92	J45, J45.0, J45.1, J45.9, J45.8, J46
All-cause anaphylaxis	995.0, 995.6, 995.60, 995.61, 995.62, 995.63, 995.64, 995.65, 995.66, 995.67, 995.69, 995.4, 989.5	T78.2, T78.0, T63.4, T88.6, T88.2
Food anaphylaxis	995.6, 995.61, 995.62, 995.63, 995.64, 995.65, 995.66, 995.67, 995.69	T78.0
Venom	989.5	T63.4
Urticaria	708, 708.0, 708.1, 708.2, 708.3, 708.4, 708.5, 708.8, 708.9	L50, L50.0, L50.1, L50.2, L50.3, L50.4, L50.5, L50.8, L50.6, L50.9
Atopic dermatitis	691.8	L20.0, L20.8, L20.9
Allergy	995.3	T78.4
Combined injury, trauma and poisoning	800 to 999, excluding 995, 978, 979	S00 to T98 excluding, T78.0, T78.2, T78.3, and T78.4

For the purpose of this study, we will only include for analysis the primary diagnosis.

*Hospitalisations for asthma after 5 years old*. Every eligible child at time zero (i.e. alive at the start of follow-up, and vaccinated with a first dose of wP or aP between 39 and 111 days old) will be included in the cohort. Where the outcome of interest is time-to-first admission to hospital for asthma after 5 years old, time zero will be the date of the fifth birthday; hospitalisations for asthma before 5 years old will be disregarded. The same rules will be applied to the time-to-recurrent event analyses.

The reasons for only including hospitalisations for asthma after 5 years of age are twofold.

Firstly, the molecular phenotypes of children with acute exacerbations of wheezing differ according to the expression of type I interferon signatures [25]. The latter have been found to be upregulated in children with wheezing episodes triggered by respiratory virus infection, but in contrast, respiratory virus negative exacerbations are characterised by the upregulation of Th_2_ associated pathways, downregulation of interferon gamma and increased likelihood of admission to hospital [25]. Unlike asthma in older children, a large proportion of wheezing episodes in preschool aged children are thought to be non-IgE mediated inflammation triggered by respiratory virus infection rather than Th_2_–mediated inflammation and airway hyperresponsiveness, and are unlikely to be prevented by wP priming.

Second, hospitalisation data for children born in NSW are only available from July 2001 and therefore, the follow-up period between the first dose of wP or aP and this time point is not available.

Admissions to hospital with asthma-related ICD codes (primary diagnosis) occurring within 14 days will be considered the same episode. Those occurring after 14 days from the previous admission will be defined as recurrent episodes.

*Hospitalisations for other atopic outcomes*. For atopic outcomes other than asthma, children born in WA will enter the cohort at 4 months old (time zero), and those born in NSW will enter the cohort at 5 years old.

Hospitalisation for the same atopic outcome occurring within 14 days will be considered the same episode of illness. Those occurring after 14 days from the previous admission will be defined as a recurrent event.

*Emergency department presentations*. For children born in WA, presentations to the emergency department for asthma and other atopic outcomes will be ascertained from the WA Emergency Department Data Collection [22], using a diagnostic hierarchy rule based on data availability, where the most specific diagnostic category is chosen over the less specific [26]. According to this rule, outcome data will be determined from the following sources: diagnosis (ICD code), symptom code, diagnosis at discharge, presenting complaint and major diagnosis category. These data are available from January 2002 to December 2013 and therefore, every model will be fitted using the date of the fifth birthday as the entry date to the cohort.

For children born in NSW, visits to the emergency department for the outcomes of interest will be sourced from the NSW Emergency Department Data Collection, which provides the principal diagnosis. These data are available from January 2005 to December 2013 and thus, time zero will be set at the age of the eight birthday. The diagnoses were recorded with either of ICD 9-CM, ICD-10-AM or SNOMED CT systems.

Presentations to the emergency department for the same atopic outcome occurring within 14 days will be considered the same episode. Recurrent presentations for the same atopic outcome will be defined as those occurring after 14 days from the previous admission.

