#### Bias in measurement of the outcome (information bias)

Concerns regarding the changes of anaphylaxis-related hospitalisation codes, their impact on epidemiologic trends, and further incomplete identification of anaphylaxis cases have been described everywhere else [52], Our study will only ascertain hospitalisations or emergency department presentations where severe IgE-mediated hypersensitivity is implied (i.e. anaphylactic shock) or those labelled as anaphylactic reaction. We expect our approach will be specific for IgE-mediated disease outcomes, but at the expense of sensitivity. Therefore, the proposed analysis plan is unlikely to fully capture the burden of IgE-mediated atopic disease morbidity since many mild cases would not have been hospitalised, or may have received alternative codes [13].

Furthermore, random errors in the identification of the outcome might be possible since ICD codes were used to determine hospitalisations for asthma and other atopic diseases. Any misclassification of the outcome will be non-differential and likely to bias toward the null. Likewise, presentations to the emergency department for the outcomes of interest may be miscoded, as diagnoses are primarily ascribed by clinical and clerical personnel at the emergency facilities who are not specialised in clinical coding.

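### The venom and all-cause anaphylaxis code lists are wider than the text's anaphylaxis-only, IgE-specific definition of these outcomes

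*Protocol article*

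**What the plan says.** Three parts of the protocol article bear on this.

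- **Outcomes, text.** The venom outcome is introduced as "anaphylactic reaction to *Hymenoptera* stings (hereafter referred as venom". Below Table 1 the article adds that "we will only include for analysis the primary diagnosis".
- **Outcomes, Table 1.** The venom row holds one code per classification, 989.5 (ICD-9 CM) and T63.4 (ICD-10 AM), without a qualifier. The all-cause anaphylaxis row ends, in ICD-9 CM, with "995.67, 995.69, 995.4, 989.5" and reads, in ICD-10 AM, "T78.2, T78.0, T63.4, T88.6, T88.2".
- **Bias in measurement of the outcome.** Ascertainment is said to be limited to encounters "where severe IgE-mediated hypersensitivity is implied (i.e. anaphylactic shock) or those labelled as anaphylactic reaction". The section continues: "We expect our approach will be specific for IgE-mediated disease outcomes, but at the expense of sensitivity".

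**The concern.** The text promises an anaphylaxis endpoint that gives up sensitivity to gain specificity. The code list does something different for two of the non-asthma outcomes. A venom code standing alone as primary diagnosis records what the child was exposed to. It does not say that the reaction was anaphylactic, and nothing else in the definition requires that. Shock due to anaesthesia is likewise not an anaphylaxis label.

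What is at stake is how a null or weak result would be read. If the all-cause anaphylaxis hazard ratio comes out near 1, a reader who trusts the specificity statement will take it as evidence about IgE-mediated disease. Part of it could instead reflect admissions that were never anaphylaxis. The article reasons this way for asthma: it leaves out preschool wheeze partly because such episodes are unlikely to be preventable by whole-cell priming. It does not apply that reasoning here.

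**Working it through.** **1. Text against code list**

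| Element | Text | Table 1 |
|---|---|---|
| Venom: type of reaction | Anaphylactic | Not specified |
| Venom: source | Hymenoptera sting | Row labelled only as venom; 989.5 / T63.4 |
| Accompanying anaphylaxis code | Implied by the ascertainment statement | Not required; primary diagnosis only |
| All-cause anaphylaxis | Anaphylactic shock or labelled anaphylactic reaction | Also 989.5 / T63.4 and 995.4 / T88.2 |

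Table 1 prints no code titles. That 995.4 and T88.2 mean shock due to anaesthesia comes from the standard classification titles, not from the article.

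**2. How Table 1 itself files these codes**

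The negative-control outcome (injury, trauma and poisoning) covers, in ICD-9 CM, "800 to 999, excluding 995, 978, 979" and, in ICD-10 AM, "S00 to T98 excluding, T78.0, T78.2, T78.3, and T78.4". Checking each all-cause anaphylaxis code against those ranges:

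- ICD-9 CM: 989.5 falls inside. All 995.x codes, including 995.4, are excluded.
- ICD-10 AM: T63.4, T88.2 and T88.6 fall inside. T78.0 and T78.2 are excluded.

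Both codes of the venom outcome therefore also count as negative-control events. This corroborates the mismatch without relying on code titles, but it does not prove it: T88.6, which by title does denote anaphylactic shock, is left inside as well.

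**3. Size of the dilution, for illustration**

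The article gives no event count, power or target effect for these outcomes, so there is no figure to reproduce. Assumptions:

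- The hazard ratio is 0.77 for true anaphylaxis. This is borrowed from the odds ratio for food allergy in the case-control study described in the Introduction.
- The hazard ratio is 1 for the other events.
- A share f of the events counted in the acellular group is not anaphylaxis.

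The observed ratio is then approximately HR = 0.77 × (1 − f) + 1 × f.

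For scale, the Schoenfeld count for 80% power at two-sided 0.05, with an assumed 1:1 split, is d = 4 × (1.960 + 0.842)² / (ln HR)².

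| f | Observed HR | Events for 80% power |
|---|---|---|
| 0 | 0.770 | 460 |
| 10% | 0.693 + 0.10 = 0.793 | 584 |
| 25% | 0.5775 + 0.25 = 0.828 | 876 |
| 50% | 0.385 + 0.50 = 0.885 | 2104 |

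The documents do not give f, so this is a range and not an estimate.

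**4. How much admission follow-up is coded in ICD-9 CM**

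NSW children enter at age 5, so from January 2002, after that state's change in July 1998: none. WA children enter at 4 months, and WA changed in July 1999. Assume uniform births over the 36 months 1997–1999, with b the month of birth.

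- Mean ICD-9 time is the average of max(0, 30 − 4 − b) = (26² / 2) / 36 = 9.4 months.
- Mean total follow-up, to the 15th birthday or December 2013, is (24 × 176 + 12 × 170) / 36 = 174 months.
- The fraction is 9.4 / 174, about 5% of WA admission follow-up.

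**The case against.** The strongest case on the other side has four parts.

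**The meaning of the codes is outside knowledge.** This is partly right. The anaesthesia-shock reading and any claim about the relative breadth of 989.5 and T63.4 rest on classification titles. The central mismatch does not: the text requires an anaphylactic reaction, and Table 1 requires only a venom code.

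**The scope is limited.** This stands. The primary asthma outcome and food anaphylaxis use none of these codes. Because food anaphylaxis is reported separately, a null composite would not be the only evidence on anaphylaxis. The article also says that outcome misclassification is likely to bias towards the null. However, what it concedes is random coding error and missed mild cases. It does not concede that the chosen codes admit other conditions, and it asserts specificity.

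**Removing the venom codes has its own cost.** This also stands. True sting anaphylaxis may be coded only to 989.5 or T63.4, and a composite without it is no longer all-cause. That argues for a second, restricted version and not for replacing the composite.

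**The dilution figures are not evidence of harm.** Agreed. They show direction and scale under a borrowed effect size.

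A reader might go further and infer that most venom admissions are non-allergic, or that the venom outcome is uninterpretable. The documents give no share, so neither follows. A reader might also infer that the change from ICD-9 CM to ICD-10 AM materially narrows the definition during follow-up. For admissions it touches only about 5% of WA follow-up and none in NSW.

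**Conclusion.** The mismatch is real and confined to two outcomes: venom and all-cause anaphylaxis. The fault is a lack of specificity relative to what the article claims; the codes are not wholly wrong. Non-anaphylactic events, if present, would move the hazard ratio towards 1 by an amount that cannot be estimated from the documents. Under the stated assumptions, 0.77 becomes 0.79 to 0.89 for shares of 10% to 50%. This assumes that the extra events are unrelated to vaccine type and, for 995.4 / T88.2, that the standard code titles apply. The point does not threaten the asthma analysis, but it changes what a null result for these two outcomes can be taken to show, and it should be settled before analysis.

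**What to change.** - Report all-cause anaphylaxis also without 989.5 / T63.4 and 995.4 / T88.2. Keep 995.0, every listed 995.6x code, T78.0, T78.2 and T88.6. Name 995.60 explicitly: Table 1 lists it under all-cause but not under food anaphylaxis, so a list built from the food row would drop it.
- Base any IgE-specific conclusion on that restricted version.
- Relabel the venom outcome as *venom-related admission (any reaction)*, with matching wording for emergency presentations.
- Correct the specificity statement in the information-bias section so that it matches the codes used.
- If counts allow, add a sensitivity analysis that counts a venom-coded admission as anaphylaxis only when an anaphylaxis code appears among the secondary diagnoses already held (up to 20 in WA, up to 50 in NSW). This departs from the primary-diagnosis rule, depends on coders having added the second code, and is feasible for admissions but not for NSW emergency data, which supply only the principal diagnosis.

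The cost is a second code list, one or two extra model runs on data already linked, and edits to the text. The restricted version will have fewer events and will omit true sting anaphylaxis recorded only under a venom code, so it should be shown beside the full composite.

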#### Hospitalisations for other atopic outcomes

We will compare rates of admission for all-cause anaphylaxis, food anaphylaxis, venom, urticaria and atopic dermatitis by means of unadjusted and adjusted Cox regression models for the time-to-first event [31], and Andersen-Gill models for recurrent events using robust standard errors to account for within-child dependence [32]. For children born in WA, the cohort entry will be set at 4 months old, and vaccination status will be treated as a time-dependent covariate. For children born in NSW, the cohort entry will be set at 5 years old. Censoring rules will be applied as above.

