The representations of the sibling effect in the literature vary widely and include birth order, the size of the sibship, or the number of brothers [46]. Although this phenomenon is supported by a number of epidemiologic studies, its underpinning mechanisms are not well understood. Briefly, increased birth order has been proposed as a proxy of frequent exposure to microorganisms, which are transmitted through unhygienic contact with older siblings during early childhood [45]. These include airway pathogens with Th_1_ and Th_17_ polarising properties, that are speculated to shift the infant’s Th_2_-biased *in utero* immunophenotype, towards allergy protective immune responses [47]. However, the sibling effect may also be a consequence of *in utero* immune programming from previous pregnancies. For example, increased birth order has been associated with lower levels of IgE in cord blood, and possibly with a lower risk of atopic sensitisation [44].

During the period of transition to aP-only doses, the receipt of wP or aP as a first dose of the primary series should have been driven by their availability in primary care centres only. Nonetheless, it is reasonable that parents would have requested the preferential administration of aP vaccine if a previous child (sibling) experienced any adverse reaction following vaccination with wP. Due to the possibility of confounding, we will include the number of previous pregnancies (a surrogate of birth order) as a variable in the models.

In addition, residual confounding that may lead to biased estimates will be approached using injury, trauma and poisoning-related ICD codes, as negative control outcomes (Table 1).

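### The negative-control outcome in Table 1 still contains study-outcome codes for venom and all-cause anaphylaxis, so a true effect on those outcomes could leak into the control

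*Protocol article*

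**What the plan says.** The section on bias due to confounding states that "residual confounding that may lead to biased estimates will be approached using injury, trauma and poisoning-related ICD codes, as negative control outcomes", and points to Table 1 for the codes. The last row of Table 1 gives the control as "S00 to T98 excluding, T78.0, T78.2, T78.3, and T78.4" in ICD-10 AM and "800 to 999, excluding 995, 978, 979" in ICD-9 CM.

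The same table lists all-cause anaphylaxis in ICD-10 AM as "T78.2, T78.0, T63.4, T88.6, T88.2". Its ICD-9 CM list ends with "995.67, 995.69, 995.4, 989.5". Venom is coded as T63.4 and 989.5 alone.

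Both are study outcomes with their own models. Under hospitalisations for other atopic outcomes, the plan reads "We will compare rates of admission for all-cause anaphylaxis, food anaphylaxis, venom, urticaria and atopic dermatitis", using Cox and Andersen-Gill regression. Nothing elsewhere in the article takes these codes out of the control.

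**The concern.** A negative control tells us about confounding only if the exposure cannot plausibly act on it. Any association seen there is then attributed to bias. Here some codes serve both purposes: they are outcomes on which the vaccine is hypothesised to act, and they are part of the outcome on which it is assumed not to act.

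If whole-cell priming did protect against venom reactions or all-cause anaphylaxis, the control would be pulled below 1 for a reason unrelated to confounding, and part of a real effect could be discounted as bias. This matters because the control is the only empirical check on residual confounding that the article describes, and the Discussion gives residual confounding as a reason for caution over any protective finding.

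The existing exclusions suggest an oversight. They remove T78.0, T78.2, T78.4 and the whole of 995, so the allergic outcomes seem meant to be out.

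**Working it through.** **Step 1: membership check.** The inputs are the Table 1 rows. Each study-outcome code was tested against the control range for its coding system, after the stated exclusions.

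| Study outcome | ICD-10 AM codes left in the control | ICD-9 CM codes left in the control |
|---|---|---|
| Asthma | none | none |
| All-cause anaphylaxis | T63.4, T88.6, T88.2 (3 of 5) | 989.5 (1 of 13) |
| Food anaphylaxis | none | none |
| Venom | T63.4 (1 of 1) | 989.5 (1 of 1) |
| Urticaria | none | none |
| Atopic dermatitis | none | none |
| Allergy | none | none |

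T63.4 appears in two rows, so there are three overlapping ICD-10 AM codes in all, not four. In ICD-9 CM the other 12 anaphylaxis codes fall under 995 and are excluded.

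**Step 2: which coding system matters.** The Introduction dates ICD-10 AM from July 1998 in NSW and July 1999 in WA. NSW admissions are linked only from July 2001, and follow-up from the fifth birthday starts in January 2002 at the earliest. ICD-9 CM admissions can therefore arise only in WA before July 1999, among children entering at 4 months. Nearly all admissions fall under the ICD-10 AM definition, the one with three overlapping codes. Some NSW emergency department records may carry ICD-9 CM codes.

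**Step 3: size of the leak.** The article gives no event counts for the control, so there is no figure to reproduce and the size must rest on assumptions. Let f be the share of control events carrying an overlapping code and HR the true hazard ratio on those codes, with no effect and no confounding on the rest:

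control HR ≈ (1 − f) × 1 + f × HR = 1 − f × (1 − HR)

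For HR, 0.77 is used for illustration. It is the odds ratio for food allergy that the Introduction quotes from the case-control study; it is not an estimate for venom or for the T88 codes.

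- f = 0.5%: 1 − 0.005 × 0.23 = 0.9989
- f = 1%: 1 − 0.01 × 0.23 = 0.9977
- f = 3%: 1 − 0.03 × 0.23 = 0.9931

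**Step 4: would the control flag it?** Assume 30,000 control events, a 50:50 vaccine split and the plan's two-sided 0.05 level. The chance of a significant result in the protective direction is

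Φ(√(30,000 × 0.25) × |ln(control HR)| − 1.96), where √(30,000 × 0.25) = 86.6.

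With no effect this is 2.5%.

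| f | Control HR, true HR 0.77 | Chance | Control HR, true HR 0.50 | Chance |
|---|---|---|---|---|
| 1% | 0.9977 | 4% | 0.995 | 6% |
| 2% | 0.9954 | 6% | 0.990 | 14% |
| 5% | 0.9885 | 17% | 0.975 | 59% |
| 10% | 0.977 | 52% | 0.95 | 99% |

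For f of 0.5% and 3% with HR 0.77, the chances are about 3% and 9%.

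**Step 5: after the correction.** With T63.4, T88.2, T88.6 and 989.5 also excluded, the overlap falls from 3 to 0 codes in ICD-10 AM and from 1 to 0 in ICD-9 CM.

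**The case against.** The strongest reply is that the overlap hardly matters. The control covers almost the whole injury and poisoning chapter, and a few codes within it are heavily diluted. On the 0.5% to 3% range the control would rarely be significant, and the article sets no rule by which so slight a shift would count as confounding. That the whole venom outcome lies inside the control does not measure the harm either; what moves the control is the share of its events that are venom. All of this stands, and it limits the size of the point.

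It can also be said that the error is cautious: it makes the control more likely to warn and cannot itself create a protective finding for a study outcome. That is largely right. However, a control that warns for the wrong reason is still a faulty diagnostic, and a protective leak could also offset confounding in the opposite direction.

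A reader might go further and infer that the two coding versions measure materially different things, because ICD-9 CM drops the whole of 995 while ICD-10 AM drops only four T78 sub-codes. The definitions do differ, but Step 2 shows that this barely touches admissions. The remaining T78 codes are not study outcomes in Table 1.

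None of this answers the definitional error. The list is stated explicitly, so this is not detail left to a fuller document.

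**Conclusion.** The point holds as a coding error of probably small effect. That the four codes are both study outcome and control follows from Table 1 alone and needs no assumption. The consequence is that a true effect on venom or all-cause anaphylaxis could be partly read as residual confounding.

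A reader might infer that a real vaccine effect would be taken for confounding. The documents do not support that. The assumed 0.5% to 3% share and the illustrative HR of 0.77 put the control within about 0.7% of 1. A visible shift needs a share of roughly 5% to 10% or more, or a large effect, and the article gives no counts to judge either. Nor does the leak reach the primary analysis through coding, since no asthma code overlaps; the same is true of food anaphylaxis, urticaria, atopic dermatitis and allergy.

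It is worth correcting because the control is the stated check on confounding and the remedy is beyond reasonable dispute.

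**What to change.** In the last row of Table 1, add T63.4, T88.2 and T88.6 to the ICD-10 AM exclusions and 989.5 to the ICD-9 CM exclusions. State the principle beside the list: no code that defines a study outcome in Table 1 may count as a control event. Excluding the rest of T78, to match the ICD-9 CM exclusion of 995, is optional.

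The cost is one edited table row and the matching line in the analysis code, with no new data. Make the change before the control is analysed, since redefining it after seeing its result would undermine its value as a check.
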